### Primary outcomes

#### Violence

We will use the Michigan Profile for Healthy Youth (MiPHY) to evaluate student outcomes related to aggression and violence, and the intermediate school district across Genesee Co. The MiPHY represents the Michigan Youth Risk Behavior Survey (YRBS), part of a nationwide surveying effort led by the Centers for Disease Control and Prevention (CDC) to monitor students’ health risks and behaviors (Michigan Department of Education, 2016). YRBS has been conducted annually by the CDC since 1993 and the psychometric properties have been evaluated and published (Brener et al., 2002; Kann et al., 2018). The MiPHY was designed to track students over time and those that move across districts. As a coordinated survey, MiPHY assesses a broad range of content related to students’ physical and mental health as well as attitudes, beliefs, and behaviors in their school, home, and neighborhood environments. Related to this project, it will include measurement of aggressive behavior, violence victimization, and bullying. The data will be maintained by GISD and provided in a de-identified format to the evaluation teams.

#### School-level discipline

The School Information System (SIS) is a web-based information system, implemented in GISD schools along with PBIS. It is designed to be an efficient, reliable, and confidential tool for collecting, summarizing, and using student discipline data, enabling school personnel to be more successful decision makers. Presently, schools in Genesee Co. report student violations and truancy via SIS, creating a standardized and comparable metric across schools in the proposed study area. We will compare treatment versus control school outcomes utilizing these data. Additional time will be allocated for more intensive analyses and linkage with MiPHY and focus group results.

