#### Restorative justice (RJ)

Restorative justice is a philosophy and process that defines crime as doing harm to people and relationships, rather than simply violating the law (Zehr, 2002). Thus, it requires consideration of the victim and community during the justice process. Although the definition continues to evolve, it has most commonly been described as “a process whereby all the parties with a stake in a particular offense come together to resolve collectively how to deal with the aftermath of the offense and its implications for the future” (Marshall, 1996). Restorative practices focus on repairing the harm caused, engaging victims and relevant school community members in the decision making process, holding offenders accountable, and preventing similar actions in the future. By focusing on accountability, fairness, and situational responses to unique events, restorative justice provides a useful framework for alternatives to zero tolerance or traditional disciplinary actions for school violence. Overall, researchers have found robust support for RJ practices, including enhanced school safety, reduced discipline problems and other behavioral referrals (Karp & Breslin, 2001; Mirsky, 2011; Stinchcomb, Bazemore, & Riestenberg, 2006).

Prior research suggests that RJ practices may have particular efficacy for youth in the age ranges targeted in this project. Researchers found, among students 14 years and younger, that youths participating in family group conferences were less likely to re-offend than youths participating in other court-ordered programs (McGarrell & Hipple, 2007). Further, offending youths, parents, and victims all expressed much more favorable perceptions of the fairness, respect, and value of the conference experience (McGarrell, 2001). Long-term follow-up of this research demonstrated that conferences following principles of “restorativeness” and “procedural fairness” were associated with reduced re-offending at 24 months and 10 years following the original conference (Hipple, Gruenewald, & McGarrell, 2014, 2015).

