### Measures

A summary of the measures is provided in Table 2.

**Table 2 Tab2:** Data sources and measures

Aim	Measures	Measure frequency	Data Sources	Original Data Sources
Primary: Intervention effectiveness on violence outcomes	Aggression, violence victimization, bullying	Fall Year 1, Spring Year 1, Fall Year 2, Spring Year 2	Michigan Profile for Healthy Youth Survey (MiPHY)^a^	Youth Risk Behavior Surveillance Survey (YRBSS)^b^ Bully-Free Schools Survey (BFSS)^c^
	Truancy, behavioral referrals	Spring Year 1, Fall Year 2, Spring Year 2	School Information System (SIS)	School Student Data
Secondary: feasibility and potential utility of implementation facilitation	Meeting agenda, interview prompts	Spring Year 1, Spring Year 2	Staff, student and 3-Person Leadership Team (3-PLT) focus groups	Questions developed by research team
	School climate, perceptions of program effectiveness (e.g., violence)	Spring Year 1, Spring Year 2	Delaware School Climate Teacher/Staff Survey^d^	Delaware School Survey - Teacher/Staff (DSS-T/S)^d^
Secondary: mechanisms and mental health	School climate scale	Fall Year 1, Spring Year 1, Fall Year 2, Spring Year 2	Delaware School Climate Student Survey^d^	Delaware School Survey - Student (DSS-S)^d^
	Anxiety, depressive symptoms, wellbeing	Fall Year 1, Spring Year 1, Fall Year 2, Spring Year 2	Michigan Profile for Healthy Youth Survey (MiPHY)^a^	Youth Risk Behavior Surveillance Survey (YRBSS)^b^
Secondary: Cost-benefit	Intervention (e.g.,materials) and imple-mentation costs (e.g., training, support)	Monthly	Time tracking by research and school staff	Data collected by research team

^a^(Michigan Department of Education, 2016), ^b^ (Kann et al., 2018), ^c^ (Lindenberger, 2005), ^d^ (Bear et al., 2016)

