### Analysis

Our primary hypothesis is that students in schools receiving the intervention will report less violence (over time) compared to students in the control group. We also hypothesize that the intervention schools have an overall lower rate of violence over the school year compared with control schools. We expect that using implementation facilitation led by a climate specialist as part of a 3-person leadership team is a feasible and sustainable approach to integrating and effectively delivering the three intervention components. Finally, we expect that students in the intervention schools will report more positive school climate compared with those in control schools and that this, in turn, will result in lower improved mental health outcomes.

A cluster randomization design is proposed with random assignment by school to one of two arms: intervention or control. Evaluation of effectiveness outcomes will involve testing at four time points: a fall of Year 1, spring of Year 1, fall of Year 2, spring of Year 2. Measures will include school records and self-report data from students and teachers. The survey of students makes use of currently collected MiPHY data. Ten schools will be recruited in the first year and 10 in the following year; staggered recruitment will allow some initial evaluation testing of the program and allow the earliest possible start time with a number of schools. Including 20 schools in the research provides an opportunity to examine school level differences. To adjust for bias introduced by multiple comparisons across our outcome variables, we will use a pair of conservative (Tukey and Bonferonni) *p*-value adjustments in addition to reporting direct effect sizes (e.g., group differences in means) to allow for assessment not dependent on standard null hypothesis testing.

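### SIS behavioral referrals serve as a primary-aim violence outcome, yet restorative justice changes disciplinary practice in one arm only, so referrals may fall without less violence

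*Protocol article*

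**What the plan says.** All references are to the protocol article.

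- **Role of the measure.** In Table 2 (Measures), the aim "Primary: Intervention effectiveness on violence outcomes" has two rows. The first holds student-reported aggression, victimization and bullying from the MiPHY survey. The second holds "Truancy, behavioral referrals" from SIS.
- **Comparison planned.** The section School-level discipline stands under Primary outcomes. It says that, at present, schools enter violations and truancy in SIS, "creating a standardized and comparable metric across schools in the proposed study area". It then commits to a contrast between arms: "We will compare treatment versus control school outcomes utilizing these data".
- **What the intervention does to discipline.** The section Restorative justice (RJ) says that "restorative justice provides a useful framework for alternatives to zero tolerance or traditional disciplinary actions for school violence". The same section names fewer behavioral referrals among the benefits found in earlier research. Study design describes RJ as acting on discipline and reward practices at the universal level, and the Discussion sets it against exclusionary discipline.
- **Primary hypothesis.** The Analysis section frames it as what students report about violence. A second hypothesis there, that intervention schools have a lower overall rate of violence, names no data source.
- **Timing.** Table 2 gives the SIS row as "Spring Year 1, Fall Year 2, Spring Year 2". The MiPHY row also has Fall Year 1.

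**The concern.** A referral count is the product of two things: how many incidents occur, and how often staff turn an incident into a recorded referral. It can stand in for violence in a comparison of arms only if the second factor is the same in both. Here one arm receives a component whose purpose is to change how staff respond to incidents. The same fight may lead to a referral in a control school and to a restorative process in an intervention school.

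The article's assurance of comparability describes present practice, before the intervention starts, and need not survive it. The article also expects RJ to lower referrals, yet it counts referrals as evidence on violence, and it says nothing on how less referring would be told apart from less violence. At stake is whether a change in disciplinary practice is credited as a reduction in violence.

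**Working it through.** The article states no figure for this outcome, so there is none to reproduce. The check has two parts.

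**1. What the text supports**

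| Step | Support in the article |
|---|---|
| Referrals sit under the violence aim | Stated, Table 2 |
| Arms will be compared on SIS data | Stated, School-level discipline |
| RJ alters the disciplinary response, in intervention schools only | Stated, Restorative justice and Study design |
| RJ has been followed by fewer referrals | Stated, Restorative justice |
| Incidents handled restoratively go unlogged in SIS | Not stated |

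The first four steps make the measure ambiguous. The last determines whether there is a bias and how large it is.

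**2. Size, as an illustration**

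Input from the article: 10 schools per arm (Sample, Schools).

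Assumptions, not in the article:
- a share q of would-be referrals is not logged in intervention schools;
- the between-school coefficient of variation (CV) of referral rates is 0.3 or 0.5;
- violence is identical in both arms.

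Formulas:
- referral rate ratio = 1 − q
- SE of the log ratio = CV × √(2/10), which is 0.134 at CV 0.3 and 0.224 at CV 0.5
- noncentrality = |ln(1 − q)| / SE, referred to a noncentral t with 18 df

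Example at q = 0.30: |ln 0.70| = 0.357. The noncentrality is 0.357/0.134 = 2.66 at CV 0.3 and 0.357/0.224 = 1.59 at CV 0.5. Against the two-sided .05 critical value of 2.10 these give 71% and 33%.

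Chance of a significant result with no effect on violence:

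| q | Ratio | CV 0.3, .05 | CV 0.5, .05 | CV 0.3, .01 | CV 0.5, .01 |
|---|---|---|---|---|---|
| 0.10 | 0.90 | 12% | 7% | 3% | 2% |
| 0.20 | 0.80 | 35% | 16% | 14% | 5% |
| 0.30 | 0.70 | 71% | 33% | 44% | 13% |

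The .01 columns assume a Bonferroni division of .05 by the five measures in the two primary rows of Table 2. The article plans Tukey and Bonferroni adjustments but does not give the divisor.

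The formula leaves out count variation within schools. A simulation that includes it (4,000 runs, 180 students per school, an assumed one referral per student-year) gives 12%/7%, 32%/16% and 66%/29% at q = 0.10, 0.20 and 0.30, unadjusted. At q = 0 it gives about 5%, the nominal level, so full logging leaves no artefact.

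**The case against.** The strongest reply is that the article nowhere says RJ takes the place of a referral. What RJ is said to replace is the disciplinary response, not the record of the incident, and SIS is described as holding student violations. If every violation is entered whatever follows, diversion does not affect the counts. A condensed article may also leave logging rules to the full protocol. This stands, and it limits the point to a conditional one. A reader might infer that RJ replaces referral, or that the metric ceases to be comparable at randomisation. The text supports only that it may.

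Second, the primary hypothesis rests on student reports, and the MiPHY items listed first in Table 2 do not pass through any staff referral decision. Teacher perceptions of violence are collected too, so a conflict between sources could be seen. This also stands: the main violence result is not exposed. It does not settle how referrals would be interpreted, because the planned linkage of SIS with MiPHY has no stated purpose and no rule covers disagreement.

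Third, the diversion shares and CVs are assumed, and multiplicity adjustment lowers the chances. That is correct, and the table shows by how much.

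Two further inferences go beyond the text. One is that an administrator on the leadership team would influence SIS entries; the article does not say who enters the records or how. The other is that the absence of Fall Year 1 from the SIS row means no baseline will exist. Table 2 lists none, but the Analysis section speaks of four time points and includes school records among the measures.

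**Conclusion.** The concern holds in conditional form. The plan uses referrals as a primary-aim violence outcome while one arm receives a component that acts on disciplinary practice and is expected to reduce referrals. A fall in referrals could then be credited as less violence, with diversion biasing the comparison in favour of the intervention.

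The size cannot be fixed from the article. It is nil under full logging. Under the stated assumptions and an unadjusted test, the chance of a spurious benefit runs from 7% (10% diversion, CV 0.5) to 71% (30% diversion, CV 0.3). The problem is confined to the SIS referral measure and does not touch MiPHY student-reported violence. It should be corrected, but it does not undermine the primary hypothesis as worded.

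**What to change.** 1. Keep MiPHY student-reported violence as the primary violence outcome, in line with the primary hypothesis in the Analysis section.
2. In Table 2, list SIS behavioral referrals as a secondary measure of disciplinary practice. Alternatively, where SIS logs violations regardless of the response, analyse violation counts in both arms instead of referrals, and state the logging rule.
3. Add to School-level discipline that a fall in referrals without a fall in MiPHY violence will not be taken as reduced violence.

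The cost is mostly wording in Table 2, School-level discipline and Analysis; using violation counts also requires confirming how SIS entries are made. The downside is that, if referrals become secondary, school records no longer give independent support to the primary violence claim, which would then rest on student self-report. The violation-count option keeps a records-based measure where the logging rule allows it.

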### Study design

See Fig. 2 for study flow diagram. In the pre-implementation phase, the project team will meet with intermediate school partners and individual schools, finalize processes and measures, secure formal agreements of study participation with schools, hire staff for the project and schedule all trainings. The current study is a cluster randomized trial in which each school will participate in the study over two years. The interventions will be staggered (5 intervention + 5 control schools starting in Year 1; 5 additional intervention and 5 additional control schools in Year 2) in order to maximize the likelihood of intensive implementation. It focuses on three key areas: (i) at a universal prevention level, focusing on changes to the physical school environment (CPTED) and promoting consistent and fair discipline and reward practices (RJ); (ii) a more targeted approach, to help those with early signs of mental health problems (MHFA); and (iii) engaging those involved in violent or aggressive situations at school through RJ practices. As noted above, the interventions are guided by a 3-PLT who seek to utilize the interventions to promote positive school climate.

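### SIS behavioral referrals count as a primary violence outcome, but restorative justice may change how intervention schools record incidents, so a difference between arms may partly reflect discipline practice

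*Protocol article*

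**What the plan says.** In Table 2 of the protocol article (Measures), the row "Truancy, behavioral referrals", with SIS as its source, stands under the aim "Primary: Intervention effectiveness on violence outcomes". The same aim holds three student-reported survey (MiPHY) measures: aggression, violence victimization and bullying. SIS is scheduled for "Spring Year 1, Fall Year 2, Spring Year 2"; the MiPHY measures also have a Fall Year 1 point.

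The School-level discipline section, under Primary outcomes, commits to comparing treatment and control schools on SIS data. Its ground for doing so is a statement about current practice: "Presently, schools in Genesee Co. report student violations and truancy via SIS", which it describes as "creating a standardized and comparable metric across schools in the proposed study area".

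On the intervention, the Restorative justice section says that "restorative justice provides a useful framework for alternatives to zero tolerance or traditional disciplinary actions for school violence". It summarizes earlier research as supporting RJ, "including enhanced school safety, reduced discipline problems and other behavioral referrals". It also counts fairness in rules and their enforcement, and peer mediation after a specific offense, among RJ practices. The Study design section gives as one of three focus areas "engaging those involved in violent or aggressive situations at school through RJ practices". The Discussion prefers this approach to exclusionary discipline. Control schools continue their usual practice.

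**The concern.** The comparability of SIS is asserted for the period before the intervention, but the trial uses SIS to compare arms after it has started. From then on, one arm has been trained to respond differently to violent incidents. A school administrator, whose school supplies the SIS data, also sits on the leadership team that delivers RJ. If some fights go to mediation in intervention schools without an SIS entry, while similar fights in control schools are entered, the recorded count falls with no change in behavior.

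The article does not fix an incident definition that is independent of the response, and it does not mention that recording could differ by arm. At stake is the reading of one component of the primary violence set: a difference in referrals could be reported as less violence when it partly shows a change in discipline practice. More schools or a better model would not remove such a bias. The cost-benefit analysis is to follow a finding of reduced violence, so a misread difference could carry into it.

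**Working it through.** **The passages side by side**

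1. Role: referrals are a primary violence measure (Table 2) with a planned comparison of arms (School-level discipline).
2. Basis for comparability: current reporting only (School-level discipline).
3. What changes after roll-out, in one arm only: the response to violent incidents (Restorative justice; Study design; Discussion).
4. Safeguards stated: linkage of SIS with MiPHY and focus group results is planned, but not as a check on recording. SIS has no Fall Year 1 point. A baseline alone would not remove a shift in recording that begins with the intervention.

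It follows that recording may differ by arm. It does not follow that it will, or by how much.

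**Illustration of size**

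The documents give no referral rate, between-school variance or power figure for SIS, so there is no stated figure to reproduce.

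- From the documents: 10 intervention and 10 control schools (Schools section); Tukey and Bonferroni adjustments across outcomes (Analysis); five measures under the primary aim in Table 2 (aggression, victimization, bullying, truancy, referrals).
- Assumed: true incident rate ratio 1; a share f of incidents in intervention schools handled without an SIS entry; no change in detection; between-school SD of log rates 0.3, 0.5 or 0.7.

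Apparent rate ratio = 1 − f. For f = 10, 20, 30 and 40% it is 0.90, 0.80, 0.70 and 0.60.

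Test: two-sided t test on log school rates, 18 df. Noncentrality = −ln(1 − f) / (SD × √(2/10)). For f = 20% and SD 0.5: 0.2231 / (0.5 × 0.4472) = 0.2231 / 0.2236 = 0.998. The critical value is 2.101 at .05 and 2.878 at .05/5 = .01.

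Probability of a significant result favoring the intervention when behavior is unchanged:

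| f | SD 0.3, .05 | SD 0.5, .05 | SD 0.7, .05 | SD 0.3, .01 | SD 0.5, .01 | SD 0.7, .01 |
|---|---|---|---|---|---|---|
| 10% | 11% | 7% | 5% | 3.2% | 1.6% | 1.2% |
| 20% | 35% | 16% | 10% | 14% | 4.8% | 2.7% |
| 30% | 71% | 33% | 19% | 44% | 13% | 6.2% |
| 40% | 95% | 58% | 34% | 81% | 31% | 14% |

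The nominal rate in that direction is 2.5% at .05 and 0.5% at .01.

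**Offset from detection**

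If the added staff raise detection by a share g, the apparent ratio becomes (1 − f)(1 + g). With f = 20%, g = 25% gives 0.80 × 1.25 = 1.00, which cancels the artefact. A larger g would bias against the intervention. The table therefore shows diversion alone, not a forecast.

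**The case against.** The strongest reply is that the causal step is inferred. RJ is described as an alternative response to an incident, whereas SIS is said to hold violations, that is, the incidents themselves. A fight sent to mediation could still be logged. The mention of fewer referrals in earlier RJ research stands beside better school safety and fits a real improvement in behavior equally well. This stands: a reader might infer that RJ itself changes when staff write a referral, but no passage says so. What remains is that nothing in the article requires logging to be independent of the response.

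The direction is also open. A climate specialist and an engaged resource officer may raise detection and so raise recorded incidents in intervention schools. This stands too. It makes the sign uncertain but does not restore comparability.

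A reader might further infer that the second hypothesis, a lower school rate of violence, would be decided by referrals. The Analysis section does not tie it to SIS; survey responses aggregated by school could serve. The first hypothesis rests on student report. The article also heads the survey measure as violence and SIS separately as school-level discipline, which goes part of the way to the distinction needed, although Table 2 then puts both under violence.

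The unadjusted false-positive rates ignore the planned multiplicity adjustment. This is fair, and the adjusted figures are shown beside them. They are lower but still exceed their nominal 0.5%.

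Finally, student report in schools that know their allocation may carry its own bias, so leaving the violence conclusion to it alone is a trade-off. For that reason the fix keeps a school-record comparison, on different entries.

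**Conclusion.** The point holds as a validity problem with one component of the primary violence set. The stated ground for comparability covers only the period before roll-out, while the intervention offers one arm another way to handle violent incidents. A difference in referrals may then partly reflect discipline practice.

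The size is unknown. With assumed inputs (unchanged behavior and detection, 20% diverted, 10 v 10 schools, SD 0.7 to 0.3), the chance of a falsely significant benefit is 10 to 35% unadjusted, or about 3 to 14% at .05/5. The net direction is uncertain.

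The documents do not support the stronger reading that the primary aim as a whole is compromised: the student-reported hypothesis does not depend on staff entries, and truancy is less exposed to this mechanism. This should be fixed; confidence is moderate, because the step from RJ to recording is an inference.

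**What to change.** 1. In Table 2 and the School-level discipline section, label SIS behavioral referrals a discipline-practice outcome, and state that a fall in them is not by itself evidence of less violence.
2. Restrict the comparability statement to the period before the intervention.
3. Have both arms log each incident in SIS before the response, RJ or other, is chosen. Base any school-record violence comparison on those response-independent entries.
4. Give the already planned MiPHY linkage a stated purpose: to check whether recorded incidents per student-reported incident differ by arm.

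Cost: one table row, a few sentences and a minor logging instruction to staff. The downside is that one non-survey measure carries less weight in the violence conclusion; the response-independent entries partly make up for it.
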